### Outcomes

The primary outcome is the proportion of any self-reported quit attempts (no smoking for at least 24 hours) in the past month at 1-month and 3-month follow-up. The secondary outcomes are self-reported 7-day point prevalence of abstinence at 1-month, 3-month and 6-month follow-up, perceived importance, confidence and difficulty to quit (scale 0–10) at all follow-up stages, proportion of using NRT in the past week or past month, and biochemically validated abstinence at 1-month follow-up.

At 1 week and 1, 3 and 6 months after recruitment, all subjects will be contacted by a trained interviewer via telephone for a survey of assessing these outcomes. After the survey, the interviewer will discuss any difficulties in quitting and using NRT with the subject. At least seven call attempts at different time points will be made before the subject is considered a loss to follow-up. Subjects who report no smoking in the past 7 days will be considered self-reported quitters. Self-reported quitters at 1 month will be invited to participate in a biochemical validation including measurement of exhaled carbon monoxide (CO) and salivary cotinine level by NicAlert® strips (http://www.nymox.com/default.action?itemid=45) near their residence. The criteria for validated abstinence were exhaled CO < 4 ppm and salivary cotinine < 10 ng/ml [33, 34].

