**Fig. 1 Fig1:**
[figure not shown]
Flow of outreach interventions. *NRT* nicotine replacement therapy

**Table 1 Tab1:** Schedule of enrolment, interventions and assessments

	Study period					
	Enrolment	Allocation	Post-allocation			
Time point	Baseline	Baseline	1 week	1 month	3 months	6 months
Enrolment						
Eligibility screen	X					
Informed consent	X					
Allocation		X				
Interventions						
Intervention group		X				
Control group		X				
Assessments						
Socio-demographic	X	X				
Daily cigarette consumption		X	X	X	X	X
Intention to quit		X	X	X	X	X
Self-reported quitting outcomes			X	X	X	X
Perceived importance, confidence and difficulty to quit			X	X	X	X
Use of NRT			X	X	X	X
Biochemically validated quitting outcomes			X	X	X	X

*NRT* nicotine replacement therapy

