### Interventions

The ambassador will help the subjects in the intervention group decide which type of NRT product (patch or gum) he/she can use and advise him/her on how to use the NRT based on his/her smoking habit and daily cigarette consumption. He/she will also be provided with an education card about NRT and a 12-page smoking cessation booklet (Fig. 1). Based on the experience of the previous trials [11, 31, 32], the choice of NRT (patch or gum) will be made according to the subject’s preference and the ambassador will provide medication counselling. Afterwards, the subjects will receive a free pack of 1-week NRT. If the subject is willing to continue the counselling at recruitment, the ambassador will introduce the NRT’s side effects, adherence and effectiveness (Table 2). Otherwise, the ambassador will contact the subject to provide such details and enquire about his/her usage of NRT by telephone within 2 days.

**Table 2 Tab2:** Counselling content for the intervention group

Part A: Introduction of NRT
1. Quitting smoking may cause withdrawal symptoms, such as irritability, insomnia, frustration, anxiety, restlessness and craving for cigarettes
2. Nicotine gum and patch can help relieve these symptoms
3. Nicotine products are far less dangerous than cigarette smoking
4. Scientific evidence strongly supports that NRT increases the quit rate and is a safe product.
Part B: Brief instruction for NRT patch
1. Apply patch on clean and dry skin on the chest, back, upper arms, hips, etc.
2. Apply one patch per day and remove before sleep
3. Change the patch site daily to avoid skin irritation
Part C: Brief instruction for NRT gum
1. Steps of chewing gum: slowly chew the gum 10–15 times → the taste gradually becomes stronger → park the gum in the buccal area for about 1–2 minutes → the taste gradually becomes lighter → repeat the above steps
2. Avoid soft drinks, coffee and fruit juice 15 minutes before chewing
3. Daily dosage should not be more than 15 pieces
Part D: Detailed instructions on NRT usage
1. Minor side effects may appear such as insomnia, skin irritation, jaw ache, hiccups and mouth soreness, but they will disappear after a few days
2. Make using NRT a daily habit
3. The standard medication period is 8 weeks. Suggest the participants continue medication after using all samples
4. Suggest the participants continue to use patch/gum even though feeling able to maintain abstinence

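### The 1-month validated-abstinence outcome requires low cotinine from everyone, so abstainers still using NRT as counselled are expected to fail it; rates are understated, and the arm comparison may be biased against the sample

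*Protocol article*

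**What the plan says.** The Outcomes section lists "biochemically validated abstinence at 1-month follow-up" among the secondary outcomes. A self-reported quitter is defined by smoking alone over the previous 7 days, so using NRT does not disqualify anyone. On testing, the text says that those who report having quit at 1 month are "invited to participate in a biochemical validation including measurement of exhaled carbon monoxide (CO) and salivary cotinine level by NicAlert" strips, and the rule is: "The criteria for validated abstinence were exhaled CO < 4 ppm and salivary cotinine < 10 ng/ml". Both parts must be met. No alternative is given for someone using a patch or gum.

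Table 2 in the Interventions section gives the counselling script. Part D states a medication period of 8 weeks and adds "Suggest the participants continue medication after using all samples" and "Suggest the participants continue to use patch/gum even though feeling able to maintain abstinence". The Background gives the standard duration as 12 weeks. Intervention subjects receive 1 week of free NRT. Control subjects receive the same advice on NRT but no sample, and are advised to buy it themselves.

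In Table 1, the row "Biochemically validated quitting outcomes" is marked at 1 week, 1 month, 3 months and 6 months. The Outcomes text places validation at 1 month only.

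**The concern.** Cotinine is a metabolite of nicotine, so patch or gum raises it whether or not the person smokes. This is general pharmacology; the article does not spell it out. The counselling asks abstainers to be on NRT at a time when the outcome rule treats nicotine exposure as evidence against abstinence. A subject who does everything the trial asks, including not smoking, is then expected to be recorded as not validated.

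Two things are at stake. The validated rate is too low in any arm that contains such subjects. And if they are more common in the intervention arm, the comparison is tilted against the treatment under test. Subjects are not blinded and the abstinence reports are their own, so the biochemical test is the trial's objective check on those reports. Under the written rule, truthful quitters who use NRT could look like misreporters. The trial is also meant to inform a larger one, so the distortion could be carried forward.

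**Working it through.** The plan gives no figure to reproduce on this point. The check has two steps.

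**1. Does the counselled NRT period cover the test?** The test is at 1 month, about 4 weeks. The counselled period is 8 weeks (Table 2) or 12 weeks (Background). Both exceed 4 weeks, so the conflict exists whichever period applies. The free sample itself covers only week 1 if used at once and continuously.

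**2. How far could the result move?** Let p be the true abstinence rate in an arm and u the share of its true abstainers on NRT at the test. Assume every current NRT user exceeds 10 ng/ml and there is no other test error. Then:

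- validated rate = p × (1 − u)
- validated RR = true RR × (1 − u_intervention) / (1 − u_control)

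Inputs:
- True abstinence of 16 % vs 8 % (RR 2.0, difference 8 points) is assumed. The article's own RR of 2.0 refers to 3-month quit attempts, not to abstinence.
- The shares on NRT are assumed. The only related figure is in the Background: 23.1 % medication use among smokers with previous quit attempts. It is used once below as a control-arm value.

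| On NRT at test, intervention vs control | Validated rates | Validated RR | Difference (points) |
|---|---|---|---|
| 0 % vs 0 % | 16.0 % vs 8.0 % | 2.00 | 8.0 |
| 30 % vs 30 % | 0.16 × 0.70 = 11.2 % vs 0.08 × 0.70 = 5.6 % | 2.00 | 5.6 |
| 30 % vs 23.1 % | 11.2 % vs 0.08 × 0.769 = 6.15 % | 1.82 | 5.0 |
| 30 % vs 5 % | 11.2 % vs 0.08 × 0.95 = 7.6 % | 1.47 | 3.6 |
| 50 % vs 10 % | 0.16 × 0.50 = 8.0 % vs 0.08 × 0.90 = 7.2 % | 1.11 | 0.8 |

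Equal use leaves the ratio intact but shrinks both rates and the difference. Unequal use moves the ratio towards the arm with less NRT use.

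With no true effect (20 % in both arms, assumed) and 30 % vs 10 % on NRT, the validated rates are 14 % vs 18 %, RR 0.78.

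For a true RR of 2.0 to fall below 1 when 10 % of control abstainers are on NRT, 2.0 × (1 − u) / 0.90 must be below 1, so u must exceed 55 % in the intervention arm.

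In people, at 50 per arm, 16 % vs 8 % is 8 vs 4 abstainers. The 30 % vs 5 % row reclassifies 8 × 0.30 = 2.4 and 4 × 0.05 = 0.2 of them.

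**The case against.** The strongest reply concerns direction and weight. Controls get the same advice, including to obtain NRT. The sample nominally ends about 3 weeks before the test, and from then on both arms have the same sources: purchase, or free supply from clinics. NRT use at 1 month could therefore be similar in the two arms, in which case the ratio is not biased. The outcome is secondary, the trial is sized for preliminary estimates, and no decision rests on validated abstinence. Occasional gum users may also stay below the cut-off, which would shrink every effect in the table.

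Most of this stands, and it limits the claim. A reader might infer that the failures fall mainly in the intervention arm, or that the rule would hide or reverse a real benefit. The documents support neither as a fact. An excess of NRT use in the intervention arm is plausible: only that arm gets free NRT, the Background suggests price as a reason for low use, and the sample may be started late or stretched. But no document gives use at 1 month by arm, and reversal needs shares for which there is no basis in the text.

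The reply does not remove the conflict between the outcome rule and the counselling. It might be said that a fuller document handles NRT users. But the article states a complete rule with both criteria required, so this is a stated rule that works badly and not a detail left out.

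A reader might also use Table 1 to argue that a 1-week test would coincide with use of the sample. The Outcomes text names 1 month only, so the mismatch is a separate point to reconcile and not evidence of bias at 1 month.

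**Conclusion.** The concern holds in a limited form. As written, the rule is expected to count true abstainers who are on NRT at 1 month as not validated, although the trial counsels that use. This understates validated abstinence in both arms to the extent that each contains such users. It biases the ratio against the sample if NRT use among abstainers is higher in the intervention arm, which is plausible but unproven.

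The size is unknown. Under the assumed true RR of 2.0, the validated RR runs from 2.0 (equal use) through about 1.8 and 1.47 to 1.11 over the shares shown. These results assume that every NRT user fails the cotinine part. The primary outcome and self-reported 7-day abstinence do not use cotinine and are unaffected. The point is worth correcting because the outcome is the trial's objective check on abstinence and the remedy is cheap.

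**What to change.** 1. Define validated abstinence in both arms as self-reported 7-day abstinence plus exhaled CO below the cut-off already stated.
2. As sensitivity analyses in all randomised subjects, report (a) the joint CO and cotinine criterion and (b) CO alone for those reporting NRT use in the past week, with CO plus cotinine for the others. Do not restrict the comparison to NRT non-users: NRT use arises after randomisation and the intervention is meant to change it, so that subset is no longer a randomised comparison.
3. Reconcile Table 1 (validation at four time points) with the Outcomes text (1 month only).
4. Reconcile the 8-week period in Table 2 with the 12-week period in the Background.

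The cost is wording and derived variables. Both markers are already measured and NRT use is already recorded; the past-week question must be asked at the 1-month call. The downside is that CO has a shorter detection window than cotinine, so some recent smoking may be missed, and not necessarily equally by arm, because subjects are unblinded. Version (b) has a related weakness: a smoker who reports NRT use faces the easier test. Showing all three versions together lets a reader see how far the result depends on the rule.

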### Sample size determination

Since the RCT will generate preliminary estimates for effectiveness of the NRT sample, we propose the sample size as 50 for each arm (i.e. total sample size = 100). A similar RCT conducted by Jardin et al. [19] which evaluated the effectiveness of 2-week free NRT to help non-motivated smokers to quit smoking was used for the power estimation. The results showed that the 3-month quit attempt rate of receiving free NRT was significantly higher than for those who only received a quitline referral (32 % vs 16 %, *p* = 0.05). The relative risk (RR) is therefore determined (32 %/16 % = 2.0). Based on the RR of 2.0 and the 100 subjects, the power and type I error for detecting the difference using the Fisher’s exact test will be 69.7 % and 0.08. Based on our recent experience with the same recruitment method and setting, the successful recruitment rate was about 15.4 % (1254/8063). We therefore estimate we have to approach 650 smokers to achieve the target sample size.

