### Statistical analyses

All data will be entered and analysed by SPSS for Windows version 20. The rate of quit attempts and 7-day point prevalence of abstinence will be assessed with the chi-square test and odds ratios of logistic regression. Continuous variables of perceived importance, confidence and difficulty to quit will be tested with repeated-measures ANOVA. Both intention-to-treat (assuming missing subjects have no changes) and complete case analyses will be done.

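### The stated 69.7 % power with type I error 0.08 is matched only by an undeclared one-sided Fisher rule; the planned chi-square test, read two-sided at 0.08, has about 56 %

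*Protocol article*

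**What the plan says.** Under Sample size determination, the article gives the trial's purpose as preliminary estimation, and on that ground "we propose the sample size as 50 for each arm (i.e. total sample size = 100"). It then takes quit-attempt rates of 32 % and 16 % at 3 months from a similar earlier trial and forms a relative risk of 2.0. From these inputs it reports two results in one sentence: "the power and type I error for detecting the difference using the Fisher’s exact test will be 69.7" (the power, in per cent), with a type I error of 0.08. No sidedness is given, and 0.08 is not labelled as a nominal level or an attained error.

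Under Statistical analyses, quit attempts and 7-day abstinence "will be assessed with the chi-square test and odds ratios of logistic regression". That is a different test, again without sidedness or level. On missing data: "Both intention-to-treat (assuming missing subjects have no changes) and complete case analyses will be done". The sample size section makes no allowance for loss.

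**The concern.** A reader will take the sentence to mean that Fisher's test, run at p < 0.08, has a 69.7 % chance of detecting a doubling of quit attempts. No Fisher test run at that cut-off has this power with 50 per arm, and the analysis section does not plan a Fisher test at all.

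Power is the only numerical support given for the sample size. If the chance of detecting the assumed effect is nearer one in two than seven in ten, a non-significant result tells the reader less than the stated power suggests. That matters because the Abstract and Discussion say that the results will help to design a larger trial.

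**Working it through.** **Inputs.** From Sample size determination: n = 50 per arm; intervention rate 0.32; control rate 0.16 (from the cited trial, since the article does not restate a control rate for its own population); Fisher's exact test; power 69.7 %; type I error 0.08. From Statistical analyses: chi-square test; missing subjects counted as unchanged in the intention-to-treat analysis. Sidedness is stated in neither section, so both forms were run.

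**Method.** Power is the sum, over all 51 × 51 outcome pairs (x, y) that the test rejects, of Bin(x; 50, 0.32) × Bin(y; 50, 0.16). Attained type I error is the same sum with one common rate in both arms. Chi-square is the uncorrected Pearson test.

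**Step 1: reproduce the printed pair.** One-sided Fisher at three nominal cut-offs:

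| Reject if one-sided p ≤ | Power | Attained error at a common rate of 16 % / 24 % / 32 % |
|---|---|---|
| 0.12 | 68.2 % | 0.077 / 0.078 / 0.082 |
| 0.121 to 0.125 | 69.74 % | 0.077 / 0.084 / 0.084 |
| 0.13 | 71.0 % | 0.078 / 0.090 / 0.086 |

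The middle row rounds to 69.7 % and 0.08. A two-sided Fisher test reaches 69.8 % only with a cut-off of about 0.24, where the attained error is about 0.15 to 0.17, so it does not give the pair.

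One-sided normal approximations at 0.08 come close without matching. With the pooled variance:
- null SE = √(2 × 0.24 × 0.76 / 50) = 0.0854
- alternative SE = √((0.32 × 0.68 + 0.16 × 0.84) / 50) = 0.0839
- z = (0.16 − 1.405 × 0.0854) / 0.0839 = 0.477, power 68.3 %

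The unpooled version gives 69.2 % and the arcsine version 68.9 %.

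**Step 2: power of the tests a reader would expect.** Exact, 32 % vs 16 %, 50 per arm:

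| Test | Nominal 0.08 | Nominal 0.05 |
|---|---|---|
| Fisher, two-sided | 47.1 % | 38.7 % |
| Fisher, one-sided | 60.1 % | not needed |
| Chi-square, two-sided | 55.7 % | 47.3 % |
| Chi-square, one-sided | 68.2 % | not needed |

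The 0.05 column is for orientation; the article states no 5 % level. The shortfall of the two-sided chi-square test at 0.08 is 69.7 − 55.7 = 14.0 percentage points. By the normal approximation, that test would need about 73 per arm to reach 69.7 %.

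**Step 3: loss to follow-up.** If a fraction L in each arm is lost and counted as no attempt, both rates are multiplied by (1 − L). The article gives no loss rate, so L is assumed, and 32 % and 16 % are taken as rates before loss. Two-sided tests at 0.08:

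| Assumed L | Rates | Chi-square | Fisher |
|---|---|---|---|
| 0 % | 32.0 % vs 16.0 % | 55.7 % | 47.1 % |
| 10 % | 28.8 % vs 14.4 % | 50.7 % | 41.9 % |
| 20 % | 25.6 % vs 12.8 % | 45.5 % | 36.6 % |
| 30 % | 22.4 % vs 11.2 % | 40.1 % | 31.1 % |

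**Step 4: precision.** 95 % confidence interval half-width for the risk difference at the assumed rates: 1.96 × √(0.32 × 0.68 / 50 + 0.16 × 0.84 / 50) = 1.96 × 0.0839 = 0.164, about 16 percentage points.

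**The case against.** The tempting stronger reading is that the printed power is an arithmetic error and that 50 per arm cannot deliver it. The document does not support that. Its sentence reports power and type I error together, as two results, which fits an attained error as well as a nominal level, and the one-sided Fisher rule in Step 1 matches both numbers. That the calculation was done this way is an inference from the match; the article does not say so. But a two-sided test at a nominal 0.08 is not stated either.

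Other points on that side also stand:
- The change from Fisher to chi-square does not itself overstate power. At the same level and sidedness, chi-square is the more powerful of the two (55.7 % vs 47.1 %).
- The article sets no 5 % level, so power at 0.05 cannot be held against it.
- The loss rates are assumed. A complete case analysis is also planned, and the dilution of rates does not apply there, although it would have fewer subjects. Whether 32 % and 16 % already count missing subjects as no attempt cannot be told from this document.
- The sample size rests first on preliminary estimation, not on a power target.

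What does not stand is that the match rescues the sentence. It requires declaring success at a one-sided Fisher p of about 0.12, a rule found nowhere in the article and well above the 0.08 printed. The directional wording of the research question does not set a one-sided test, and the chi-square test named for the analysis is ordinarily two-sided.

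**Conclusion.** The concern holds in a limited form. The printed pair can be obtained from the article's own inputs, but only under an undeclared one-sided Fisher rule with a nominal cut-off of about 0.12, and it does not describe the planned analysis. For the chi-square test read two-sided at 0.08, power is about 56 %, some 14 points lower. Loss counted as no attempt would lower it further, by an amount that depends on the loss rate.

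This rests on three assumptions: a control rate of 16 % carried over from the cited trial, the ordinary two-sided use of chi-square, and 0.08 as its nominal level.

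A reader might also infer that the trial is too small for its purpose, or that the larger trial would be planned on a false premise. Neither follows: the stated purpose is preliminary estimation, and the later trial would draw on the results, not on this power figure. Severity is moderate.

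**What to change.** Rewrite the power sentence and keep n = 100:
- State whether the test is one- or two-sided, and whether 0.08 is a nominal level or an attained error.
- Name the same test, sidedness and level under Sample size determination and Statistical analyses.
- Restate the power for that test. If it is the two-sided chi-square at 0.08: about 56 % for 32 % vs 16 %, before loss to follow-up.
- Say that loss counted as no attempt reduces this, and give the loss rate assumed.
- Present the trial as estimation, with a 95 % confidence interval half-width of about 16 percentage points for the difference in quit-attempt rates.

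If a one-sided rule was intended, declare it with its actual p cut-off and use it in the analysis as well.

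The cost is wording only. No subjects are added, and on the two-sided reading the stated power becomes less favourable.

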### Randomization

The individual randomization method by SNOSE will be used to ensure the allocation sequence is concealed from both ambassadors and participants before the group allocation [35, 36]. The primary investigator will prepare about 150 identical, opaque, sealed, A5-sized envelops, with a unique three-digit serial number on the cover of each envelope as an identifier. Half of the envelopes will each contain an eligibility form, an education card of NRT and an action plan for the intervention group. The remaining half will contain the same eligibility form and education card, and an action plan for the control group. After inserting the intervention materials in the envelopes, they will be shuffled and then numbered. When the subject consents to participate, the ambassadors will open one envelope according to the sequence of the serial number and assign the treatment condition based on the action plan.

### Allocation concealment

The group allocation will not be known by the subjects and the ambassador before the assignment allocation. In reality, smokers often linger and smoke for just about a few minutes at the hotspots, and then leave. Also, there are far more smokers than ambassadors in our selected outdoor hotpots. Therefore, the smokers may not notice the procedures of the enrolment of other subjects clearly. In addition, not all smokers want to be approached by strangers, and finally very few of them will agree to participate in the RCT, which is expected. Therefore, our ambassadors can rarely approach and recruit a new subject quickly after finishing the enrolment of a previous subject. It is unlikely that their decision to join the RCT is greatly influenced by what they have observed from others’ enrolment and intervention. Although the control group subjects may see that other subjects receive the NRT sample, the impact on the enrolment and group allocation is limited in reality.

